##### 2.1.4.3 Withdrawal criteria

•Deviation from the assigned anesthesia protocol.•Occurrence of any serious adverse event.•Intraoperative administration of heart rate-altering medications (e.g., atropine).•Failure to complete all required monitoring procedures.

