### 2.3 Sample size calculation

This study is a randomized controlled trial aiming to compare the effects of TENS and taVNS in foraminoscopy. According to relevant research, with the VAS as the primary outcome indicator, the standard deviation of taVNS is 2.5, and that of TENS is 3.0. Calculated using PASS software, the minimum sample size required for each group is 121. Considering a dropout rate of 10%–15%, to ensure the statistical power and the reliability of the results, the final sample size of each group is adjusted to 136 people. Each subgroup was allocated 32 participants, and a total of 272 participants are recruited.

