##### 2.4.2.1 Observation indicators

Record the changes of corresponding indicators at different time points:

•Time 1: 5 min after the patient enters the operating room, before electrical stimulation.•Time 2: Before the operation, 30 min after the electrical stimulation upon entering the room.•Time 3: Immediately at the start of the operation.•Time 4: 0.5 h after the start of the operation.•Time 5: 1.0 h after the start of the operation.•Time 6: 1.5 h after the start of the operation.•Time 7: 2.0 h after the start of the operation.•Time 8: At the end of the operation.

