### 3.3 Methods in analysis to handle protocol non–adherence and any statistical methods to handle missing data

Intention-to-treat analysis will be used, and missing data will be appropriately processed in accordance with established guidelines.

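### Incomplete monitoring is a withdrawal criterion with no tolerance, although the schedule fixes readings up to 2.0 h that a shorter operation cannot supply; this conflicts with the stated intention-to-treat analysis

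*Protocol article*

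**What the plan says.** All references are to the protocol article.

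- **Withdrawal.** Section 2.1.4.3 names four grounds for withdrawal. The last is "Failure to complete all required monitoring procedures". No number of permitted gaps and no exception is given.
- **Schedule.** Section 2.4.2.1 sets T4 to T7 at 0.5, 1.0, 1.5 and 2.0 h from the start of surgery; the latest of these is "Time 7: 2.0 h after the start of the operation". The close of surgery is a separate point, "Time 8: At the end of the operation". Table 1 (section 2.5.3) marks VAS, BIS, MOAA/S, Ramsay and HRV at every one of T1 to T8. Neither place says what happens to T4 to T7 if surgery has already ended.
- **Analysis set.** Section 2.4.2.1.1 keeps the recent data of a subject who leaves midway or is dissatisfied with the analgesia, under intention-to-treat. Section 3.3 repeats intention-to-treat and adds that "missing data will be appropriately processed in accordance with established guidelines".
- **Numbers.** Section 2.3 says that "the minimum sample size required for each group is 121". After an allowance of 10% to 15% for dropout, "the final sample size of each group is adjusted to 136 people".

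**The concern.** Taken literally, the withdrawal rule catches a patient who loses one BIS value or one ECG segment, and every patient whose operation ends before 2.0 h. Both arise after randomisation. Both may depend on pain and cooperation, which the stimulation is meant to change. If such patients left the comparison, those remaining would be the long and fully recorded operations, and the two groups would no longer be protected by randomisation.

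The design makes it hard to see what else the withdrawal could do. Stimulation is given for 30 min before surgery (section 2.4.2), so none is left to stop once the operation begins. Table 1 marks no assessment after T8, and section 4.1 says there is no long-term postoperative follow-up. Completeness of monitoring is known only at T8. Withdrawal on this ground therefore has little practical effect except on the patient's data, where it meets the intention-to-treat statements head on.

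**Working it through.** **1. Number of readings.** From Table 1: 5 measures × 8 times = 40 per patient. T7 alone accounts for 5.

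**2. The plan's own sample size.** Section 2.3 gives SDs of 2.5 and 3.0 and section 3.1 a two-sided α of 0.05. No target difference or power is stated. *Assuming* a 1.0-point VAS difference and 80% power:

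- Normal approximation: n = (1.960 + 0.842)² × (2.5² + 3.0²) / 1.0² = 7.849 × 15.25 = 119.7, so 120 per group.
- With the noncentral t distribution (Welch), 121 per group gives power 0.801.

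So 121 is reproduced, but only under these two assumptions.

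**3. The margin for loss.** 136 − 121 = 15, and 15/136 = 11.0%. Inflating 121 by division: 121/0.90 gives 135, 121/0.89 gives 136 and 121/0.85 gives 143. The 136 therefore covers about 11% loss, near the lower end of the stated 10% to 15%.

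**4. When the margin would be exceeded, if affected patients were excluded.**

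*(a) Short operations.* If a share f ends before 2.0 h, 136 × (1 − f) remain. The values of f are assumptions. Power assumes the 1.0-point difference.

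| f | left per group | power |
|---|---|---|
| 10% | 122.4 | 0.81 |
| 20% | 108.8 | 0.76 |
| 30% | 95.2 | 0.70 |
| 50% | 68.0 | 0.55 |

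The break-even is f = 11.0%.

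*(b) Missed readings.* The share of patients with at least one gap depends on how misses cluster. If all 40 readings are missed independently with probability p, the share is 1 − (1 − p)^40. If a miss takes out a whole time point, all five measures together, it is 1 − (1 − p)^8. The values of p are assumptions.

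| p | independent, 40 readings | whole time point, 8 points |
|---|---|---|
| 0.5% | 18.2% (111 left) | 3.9% (131 left) |
| 1% | 33.1% (91 left) | 7.7% (125 left) |
| 2% | 55.4% (61 left) | 14.9% (116 left) |

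The break-even is p = 1 − (121/136)^(1/40) = 0.29% for independent misses, and 1 − (121/136)^(1/8) = 1.45% for whole time points.

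**5. The rules side by side.** Section 2.1.4.3 withdraws a patient for a missing reading. Sections 2.4.2.1.1 and 3.3 keep patients and process what is missing. The article does not say which prevails for a patient withdrawn on this ground. Section 2.4.2.1.1 speaks of a subject who leaves midway or is dissatisfied, not expressly of one withdrawn because a reading is absent.

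**6. If intention-to-treat prevails.** Section 3.1 plans repeated-measures ANOVA for changes over time. In its classical form this needs a value at every time from every subject. A patient without T7 would drop out of that analysis even though no one had been withdrawn.

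**The case against.** The strongest reply is that withdrawal is not exclusion. Section 2.1.4.3 nowhere says that a withdrawn patient's data are discarded, and sections 2.4.2.1.1 and 3.3 point the other way. This stands. A reader might infer that short-operation patients are removed and that the trial becomes a complete-case set, but the document does not say so. Nor can it be said that the missing-data statement in section 3.3 would have nothing to act on: under intention-to-treat, these are the very patients whose data are missing.

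A second reply is that a reading due after surgery has ended is not naturally a required one. The floating T8 shows that the authors expected operations of varying length. This is a fair reading, but the article never states it, and the withdrawal rule turns on the word.

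A third reply concerns size. Independence across 40 readings is implausible, because the five measures are scheduled together. With whole-time-point misses at 1%, about 8% of patients are affected rather than 33%, and the group stays above 121. This also stands.

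Finally, a journal article may leave the details of missing data to a fuller document. That excuses the brief wording of section 3.3. It does not excuse two rules within the article that pull in opposite directions.

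**Conclusion.** The point holds as an unresolved conflict. A withdrawal rule without tolerance, attached to a fixed schedule that some operations may be unable to complete, stands against a stated intention-to-treat analysis. If the rule reaches the data, it selects patients on events after randomisation. That bias is the main risk, and it does not depend on the sample-size arithmetic.

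A reader might go further and conclude that the dropout allowance is overrun and power lost. The documents do not support that. Overrun requires that more than 11.0% of a group be affected *and* excluded. Neither the distribution of operation length nor the rate of missed readings is given, and exclusion is not stated. The power figures also rest on a 1.0-point difference that the plan does not name.

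The margin is nevertheless thin, and may be thinner. Section 2.3 also says "Each subgroup was allocated 32 participants, and a total of 272 participants are recruited". With a control and three stimulation subgroups in each group (section 2.2), 4 × 32 = 128, not 136. If 128 were randomised per group, only 7 losses (7/128 = 5.5%) would be covered. That mismatch is a separate matter.

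**What to change.** 1. In section 2.1.4.3, delete incomplete monitoring as a withdrawal criterion, or state that it never removes a patient from the analysis. The other withdrawal criteria are not touched by this point.
2. In section 2.4.2.1 and as a footnote to Table 1, state that T4 to T7 are taken only while the operation is in progress, and that a time point not reached is not applicable and is no deviation.
3. In section 3.3, state that every randomised patient is analysed in the assigned group with the readings obtained, in line with section 2.4.2.1.1.
4. In section 3.1, replace classical repeated-measures ANOVA with a method that keeps patients who lack late readings, such as a linear mixed model.

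The cost is one line deleted, one footnote and two sentences of analysis text. No patients, visits or procedures are added.

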#### 2.1.5 Who will take informed consent?

Data collection will only start after the subjects sign the informed consent form, and the assessment personnel will explain this.

#### 2.1.6 Additional consent provisions for collection and use of participant data and biological specimens

Biological specimens will not be collected in this experiment.

### 2.2 Randomization and blinding

Patients are divided into two groups (TENS group and taVNS group) through a random number table generated by a computer. Each group is designed with a control group and three stimulation subgroups. A double–blind design is adopted, and neither the interveners (personnel implementing electrical stimulation interventions) nor the patients are aware of the grouping situation. They do not have access to the group allocation sequence, are not involved in randomization procedures, and do not participate in outcome assessments. To ensure effective blinding, all electrode pads will be covered with identical opaque adhesive membranes, with only the conductive contact point exposed. Additionally, electrode pads will be applied to both the auricular and acupoint regions in all participants, regardless of group allocation. As a result, the interveners will not know which site is actively receiving stimulation.

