#### 2.4.2 Intervention description

Based on a systematic review and related studies (23), each group receives 30-min corresponding stimulation or placebo intervention before surgery. The current intensity is adjusted to the maximum tolerance of the patient, the pulse width is fixed at 200 μs, and the frequency is fixed at 30 Hz. When patients with severe pain cannot tolerate it, oliceridine fumarate injection is supplemented to the subjects. The supplementary standard is: a single dose of 0.35 mg–0.50 mg, intravenous injection, and the dosing interval is not less than 6 min.

•TENS Group: Electrodes are placed at the bilateral Neiguan and Hegu acupoints of the subjects. Hegu (LI4): Located on the dorsum of the hand, between the 1st and 2nd metacarpal bones, at the midpoint of the radial side of the second metacarpal bone. Neiguan (PC6): Located on the palmar aspect of the forearm, 2 cun proximal to the transverse wrist crease, between the tendons of the palmaris longus and the flexor carpi radialis muscles.•TaVNS Group: Electrodes are placed at the bilateral tragus of the subjects.

Each stimulation group was further subdivided into following stimulation modes:

•Continuous Wave Group: Given 30-min continuous electrical stimulation.•Intermittent Wave Group: Subjects receive 30-min intermittent electrical stimulation (stimulate once every 15 s, with an interval of 5 s).•Dense-Sparse Wave Group: Subjects receive 30-min variable–frequency electrical stimulation (sparse wave 6 Hz, dense wave 30 Hz).•Control Group: Electrode patches are placed but not energized, making the patients psychologically believe that they have received stimulation.

The experimental process is shown in Figure 1.

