## 3 Statistical analysis methods

### 3.1 Statistical methods for primary and secondary outcomes

This study will use SPSS 20.0 and PhysioZoo software for statistical analysis. The significance level of all statistical tests is set at α = 0.05, and two-sided tests are performed. For the differences in different intraoperative indicators such as pain score VAS, anesthesia depth BIS, and heart rate variability HRV between the trans-auricular vagus nerve stimulation group (taVNS group) and the transcutaneous peripheral nerve stimulation group (TENS group), an independent-samples *t*-test is first performed. If the data do not meet the normal distribution, the non-parametric test method Mann–Whitney U test will be used for comparison between the two groups. For the comparison between different subgroups (different stimulation modes) within each group, one-way analysis of variance will be performed to compare the differences in various indicators. If the data do not meet the assumptions of analysis of variance, the Kruskal–Wallis H test will be used as a non-parametric alternative method. At the same time, for multiple-measurement data, repeated-measures analysis of variance (Repeated Measures ANOVA) will be used to compare the changes of indicators at different time points within the same group. To further evaluate the impact of different influencing factors (such as stimulation mode) on intraoperative analgesia and sedation effects, multiple linear regression analysis will be used to help identify their relationships with various indicators.

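### The TENS and taVNS groups each contain an un-energised control, so the whole-group t-test dilutes the active contrast by about a quarter, and leaving the controls out falls short of the stated 121 per group

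*Protocol article*

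**What the plan says.** - **Groups.** Section 2.2 randomises patients to a TENS group and a taVNS group, and adds: "Each group is designed with a control group and three stimulation subgroups". Section 2.4.2 lists the control as one of four modes within each stimulation group: "Electrode patches are placed but not energized, making the patients psychologically believe that they have received stimulation".
- **Electrodes.** Under section 2.2, "electrode pads will be applied to both the auricular and acupoint regions in all participants, regardless of group allocation".
- **Sample size.** Section 2.3 sizes the TENS versus taVNS comparison "with the VAS as the primary outcome indicator". It gives the inputs as "the standard deviation of taVNS is 2.5, and that of TENS is 3.0" and concludes that "the minimum sample size required for each group is 121", raised to 136 for 10%–15% dropout. It then divides the groups into subgroups of 32, with 272 patients in total. It states no mean difference and no power.
- **Test.** Section 3.1 compares VAS, BIS and HRV "between the trans-auricular vagus nerve stimulation group (taVNS group) and the transcutaneous peripheral nerve stimulation group (TENS group") by an independent-samples t-test, with Mann–Whitney as the fallback. It does not say that control patients are left out. Subgroups within a group are compared by one-way ANOVA, and a multiple linear regression on factors such as stimulation mode is also planned.

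**The concern.** The named groups are mixtures of three energised subgroups and one that gets no current. The two un-energised subgroups have the same pads at the same sites, so no true difference between them is expected. Including them in the comparison pulls the expected group difference toward zero. The sample size uses one standard deviation for taVNS and one for TENS and makes no visible allowance for sham patients, although the 136 per group is then split into subgroups that include them.

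The stake is the trial's main question. A real difference between the two techniques could be missed, and a non-significant whole-group result could be taken as evidence that the techniques perform alike.

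**Working it through.** **Inputs.** From section 2.3: SDs 2.5 and 3.0, 121 evaluable and 136 recruited per group, subgroups of 32 (136/4 = 34 if the group total is taken instead). From section 3.1: two-sided α = 0.05. Not stated, so assumed: target power 80% to 90%, with the difference that each implies at 121.

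**1. The plan's own figure.** Variance sum = 2.5² + 3.0² = 15.25. With n per group = 15.25 × (z₀.₉₇₅ + z_power)² / δ²:

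- 80% power: 15.25 × (1.960 + 0.842)² = 119.7. At n = 121, δ = √(119.7/121) = 0.995.
- 90% power: 15.25 × (1.960 + 1.282)² = 160.2. At n = 121, δ = √(160.2/121) = 1.151.

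The figure of 121 cannot be reproduced from the stated inputs alone. With δ = 1.0 and 80% power, the normal formula gives 120 and the unequal-variance (Welch) noncentral t gives exactly 121 (power 80.1%). A 90% plan with δ of about 1.15 fits as well.

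**2. Dilution.** The sham share is 32/128 = 34/136 = 1/4. Expected whole-group difference = ¾ × δ + ¼ × 0 = 0.75δ.

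**3. Power of the whole-group test**, SDs held at 2.5 and 3.0 (Welch and normal formula agree to within about half a percentage point):

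| Plan | δ | 0.75δ | Power at 121 | Power at 136, no dropout | n per group to regain target |
|---|---|---|---|---|---|
| 80% | 1.0 | 0.75 | 56% | 61% | 213–214 |
| 90% | 1.151 | 0.863 | 68% | 73% | 216 |

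The loss depends only on the target power, not on the unknown δ. In the normal approximation, the 80% plan has z-sum 2.802; 0.75 × 2.802 = 2.101, and Φ(2.101 − 1.960) = 56%. For the 90% plan, 0.75 × 3.242 = 2.431, and Φ(2.431 − 1.960) = 68%. The required n rises by 1/0.75² = 1.78.

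**4. The other reading: controls left out.** Active patients recruited per group: 3 × 32 = 96 or 3 × 34 = 102. Of 121 evaluable, 0.75 × 121 ≈ 91 are active.

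| Active n per group | Power, δ = 1.0 | Power, δ = 1.151 |
|---|---|---|
| 102 | 73% | 84% |
| 96 | 70% | 82% |
| 91 | 68% | 80% |

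Even before dropout, 96–102 is below 121.

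**5. What the active patients can detect** (Welch):

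| Active n per group | 80% power | 90% power |
|---|---|---|
| 102 | 1.09 | 1.26 |
| 91 | 1.15 | 1.33 |

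**The case against.** The strongest reply is that pooling the controls into the t-test is inferred. Section 3.1 does not say that they are in. The abstract speaks of three stimulation modes and no control, and section 3.1 glosses the subgroups as stimulation modes. The exact analysis set is often left to an analysis plan, which is not shown here. This stands as far as it goes: the article does not state the pooling in words, and a reader should not report it as explicit. But the groups as defined in sections 2.2 and 2.4.2 contain the controls, and the alternative reading does not rescue the design. An analysis plan that excludes the controls cannot supply the active patients missing from the 121.

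A second reply is that the planning difference is unknown and might already refer to whole groups. In that case there is no further loss of power, although the test would still estimate a diluted contrast. The power figures are therefore conditional and are given for both an 80% and a 90% plan.

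Three stronger readings are tempting and are not supported:

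- *The test is invalid.* It is not. The comparison of randomised groups keeps its type I error. What changes is the quantity estimated.
- *Active versus sham is examined only through the omnibus ANOVA.* The planned regression on stimulation mode could also estimate each mode against control. How well powered such contrasts are cannot be said, because the article gives no difference for them.
- *Keeping the two controls apart is an error.* A control within each arm is legitimate. Combining identical controls gains efficiency but corrects nothing.

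**Conclusion.** The point holds: the sample size and the design do not fit together, whichever way the TENS–taVNS test is read. With controls in, the test targets about 75% of the active difference; if 121 was sized on that difference, power drops from 80% to about 56%, or from 90% to about 68%. With controls out, the active patients number 96–102 per group against a stated minimum of 121, with power before dropout of 70–73% on the 80% plan and 82–84% on the 90% plan.

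The 75% rests on equal subgroups and on no true difference between the two controls, which the pad placement supports. The power figures also rest on an assumed 80%–90% target and on the planning difference and SDs describing active stimulation. Holding the SDs fixed is slightly generous, since mixing energised and sham patients adds variance.

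**What to change.** 1. In section 3.1, define the primary TENS versus taVNS contrast on energised patients only, with the three modes pooled at each site.
2. In section 2.3, state the planning difference and the power, and restate them for the active patients available: 96–102 randomised and about 91 evaluable per group, giving 80% power for a difference of about 1.09–1.15 VAS points, or 90% for about 1.26–1.33. In the same edit, settle whether a subgroup is 32 or 34, since 4 × 32 = 128, not 136.
3. Optionally, combine the two identical control cells into one common control, and pre-specify taVNS versus sham and TENS versus sham as contrasts alongside the planned ANOVA and the regression on stimulation mode.

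The cost is wording in two sections. No extra patients are needed, but the stated power or detectable difference will look less favourable than 121 per group implies.

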###### 2.4.2.1.2 Strategies to improve adherence to interventions

Before the surgery, explain the exact effects of the electrical stimulation–related therapies to the patients who have signed the informed consent form to reduce their preoperative fear and tension.

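### The double-blind claim does not hold for active versus sham or for the active site, because the masking hides appearance while current is set to maximum tolerance and sham pads carry none

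*Protocol article*

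**What the plan says.** Section 2.2 (Randomization and blinding) states that "neither the interveners (personnel implementing electrical stimulation interventions) nor the patients are aware of the grouping situation". It describes two masking measures. The first is that "all electrode pads will be covered with identical opaque adhesive membranes, with only the conductive contact point exposed". The second is that "electrode pads will be applied to both the auricular and acupoint regions in all participants, regardless of group allocation". From these it concludes: "As a result, the interveners will not know which site is actively receiving stimulation". It adds that the interveners "are not involved in randomization procedures, and do not participate in outcome assessments". The abstract also calls the trial double-blind.

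Section 2.4.2 (Intervention description) sets the stimulation: "The current intensity is adjusted to the maximum tolerance of the patient". The active site is the wrist and hand in the TENS group and the tragus in the taVNS group. For the control cell of each group: "Electrode patches are placed but not energized, making the patients psychologically believe that they have received stimulation". The same section makes supplementary oliceridine depend on severe pain that the patient cannot tolerate.

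Section 2.4.2.1.2 says that staff will, before surgery, "explain the exact effects of the electrical stimulation"-related therapies to consenting patients, in order to reduce fear and tension.

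**The concern.** Both masking measures act on what can be seen. Neither acts on what can be felt, yet the intensity rule makes sensation the strongest cue in the trial. A current at the limit of tolerance is perceptible by definition, and that limit can be found only from the patient's response.

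VAS is self-reported, is a primary indicator (section 2.5.1) and is the outcome used for the sample size (section 2.3). Rescue oliceridine also depends on the patient's expressed pain. If patients know whether they received current, a difference between energised and control cells on either measure mixes the effect of stimulation with expectation. Readers who accept the double-blind label would not allow for this.

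**Working it through.** The plan gives no figure for this point, so the check sets the two sections side by side.

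**What each measure can hide**

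| Cue | Opaque covers | Pads at both sites | Left open by section 2.4.2 |
|---|---|---|---|
| Pad appearance and placement | hidden | hidden | no |
| Whether current flows | not hidden | not hidden | yes: maximum tolerance versus no current |
| Ear or wrist/hand, if energised | not hidden | not hidden | yes: felt at one site |
| Waveform | not hidden | not hidden | partly: a patient may not be able to name it |
| Parent group of a sham patient | hidden | hidden | no: the same pads and no current in both groups |

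**Patients.** Energised patients feel current, and feel it at one site. Control patients have no current to feel and no tolerance level to find. Nothing described masks sensation, and no check of blinding is described.

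**Interveners.** The document does not say who adjusts the current. It defines interveners as the staff implementing stimulation, so it is a close inference that they do. Finding maximum tolerance needs the patient's feedback, so whoever does it very probably learns active versus sham and the site. The conclusion drawn in section 2.2 does not follow from the measures given for it.

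**How many patients.** There are 2 groups × 4 cells = 8 cells. The total of 272 gives 272/8 = 34 per cell, hence 2 × 34 = 68 control and 6 × 34 = 204 energised patients. Section 2.3 also states 32 per subgroup, which gives 8 × 32 = 256, hence 64 and 192. The two do not agree, but the argument is the same under either.

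**Illustration under an assumed bias.** The document gives no size for expectation bias. Assume no true effect and a pure reporting shift of b VAS points in all three energised cells against control. Use the SDs in section 2.3 (taVNS 2.5, TENS 3.0), 34 per cell and two-sided 5%.

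- Pooled active versus sham: SE = SD × √(1/102 + 1/34). For taVNS this is 2.5 × 0.198 = 0.495. At b = 0.5, b/SE = 1.01, and the rejection rate is 1 − Φ(1.96 − 1.01) + Φ(−1.96 − 1.01) = 17.3%.
- Four-cell one-way ANOVA, the test in section 3.1: noncentrality = 34 × 0.75 × b²/SD², with 3 and 132 df. For taVNS at b = 0.5 this is 34 × 0.75 × 0.25/6.25 = 1.02, and the rejection rate is 11.5%.

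| Assumed b | taVNS pooled | TENS pooled | taVNS ANOVA | TENS ANOVA |
|---|---|---|---|---|
| 0.25 | 8.0% | 7.1% | 6.5% | 6.0% |
| 0.5 | 17.3% | 13.4% | 11.5% | 9.4% |
| 1.0 | 52.4% | 39.1% | 35.5% | 25.4% |

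With 32 per cell the rates are slightly lower (taVNS at b = 0.5: 16.5% pooled, 11.1% ANOVA). The table shows sensitivity to an assumption and does not estimate the bias.

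**The case against.** The strongest defence is that the article condenses a fuller protocol, and that the titration procedure and what patients are told about sham may be set out there. That would answer a complaint about missing detail. It does not answer this point, because the article gives its masking mechanism and draws a conclusion that its own intensity rule undercuts.

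Several stronger readings are tempting, and the document does not support them:

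- **That patient and operator learn the full allocation.** Allocation is one of eight cells. Sham patients in the two groups have the same pads and no current, so their parent group can stay masked, and the exact waveform may too.
- **That an unblinded operator could bias the scoring.** Section 2.2 says interveners take no part in outcome assessment, and no section gives them a role in rescue. The main harm runs through the patient.
- **That control patients have been told what they should feel.** Section 2.4.2.1.2 speaks of effects and of reducing fear. It does not say that sensations are described.
- **That the bias can be expressed as a share of the planned difference.** Section 2.3 states no difference and no power. Any difference recovered from it concerns TENS versus taVNS, which is not the active-versus-sham contrast.

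The scope is also limited. The sized and first-listed comparison is TENS versus taVNS, with one control cell of four in each group. The control cell enters the within-group subgroup comparisons. BIS and HRV are recorded by instrument and are less open to expectation.

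**Conclusion.** The stated double-blind property fails for active versus sham and for the active site. This rests on two inferences: a current at maximum tolerance is felt while an unenergised pad is not, and the person setting the current is an intervener. The patient side needs only the first.

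The consequence is greatest for VAS and rescue oliceridine in the within-group comparisons that include the control cell. Active TENS versus active taVNS is less exposed because both are felt, but it is not free of bias, since patients know the site. The size cannot be derived from the document, and the rates above depend entirely on the assumed shift.

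**What to change.** 1. Reconcile sections 2.2 and 2.4.2, and the label in the abstract. Either describe how sensation is masked, or drop double-blind and state which roles are actually blind.
2. Specify that those who score VAS, MOAA/S and Ramsay, and those who decide on oliceridine, are kept away from the stimulation period and the stimulator settings. Use the term assessor-blinded only if this is done. Section 2.2 separates interveners from assessment but never says that assessors are blind.
3. Record each patient's allocation guess at T2, after that time point's VAS and before the operation starts, and report it by cell.
4. State that active-versus-sham contrasts on VAS and rescue use are open to expectation bias, and that active TENS versus active taVNS is less so but not free of it.

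A trial run of current at both sites in every patient would not be a simple remedy. It would give real current to sham patients and comparator-site current to active patients, and the later absence of current might become more obvious.

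The cost is one extra question per patient, arrangements to keep scorers and rescue deciders apart from the stimulation, and a less favourable blinding label. The allocated programmes and the sample size do not change.
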